##### Compliance definition

This study will collect the date and time associated with each of these four measures: (1) when serum lactate level was collected, (2) when blood culture was collected, (3) when antibiotics were started, and (4) when fluids (30 ml/kg crystalloids) were started. Compliance is defined as to whether or not these date and time stamps were within 1 or 3 h (inclusive) of time zero depending on hospital randomization.

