### Study objectives

The study aims are as follows: (*Aim 1*) Examine comparative effectiveness of the 1-h versus 3-h sepsis bundle on the primary outcome of hospital mortality and secondary outcomes of length of stay, ventilator-free days at 28 days, and rate of acute respiratory failure requiring mechanical ventilation. *Hypothesis:* The 1-h bundle will have lower hospital mortality. (*Aim 2*): Conduct a mixed methods evaluation of a multi-faceted implementation strategy to enhance compliance with the 1 and the 3-h bundles. *Hypothesis*: 1 and 3-h bundle implementation compliance will be similar as assessed by (a) the electronic health record (EHR), (b) surveys of key informants regarding implementation climate, organizational readiness for change, and implementation leadership, (c) recordings of learning collaborative meetings, and (d) interviews with participants. (*Aim 3*): Determine if clinical sepsis phenotypes determined by characteristics measured at presentation modify the treatment effect of the 1 or 3-h bundle. *Hypothesis:* Routine clinical information available at ED presentation will identify phenotypes more likely to benefit from the 1 or 3-h bundle.

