#### Aim 2: Quantitative analysis will demonstrate improved compliance in both arms through the implementation strategy and qualitative analyses will provide insights into implementation strategy effectiveness

Surveys assessing implementation-related constructs will be completed at baseline (Exploration phase) and then repeated during the Sustainment phase. We will conduct within-subjects Wilcoxon signed rank test with the survey data, examining changes over time.

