##### Quantitative analysis of bundle compliance

Bundle compliance will be defined as all-or-nothing for the individual elements of the bundles. The statistical analysis will be similar to the primary analysis for hospital mortality.

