### Design considerations

Several key design considerations for this study warrant discussion. First, we chose to compare the 1-h to the 3-h bundle. We could have proposed separate trials for 1- and 3-h bundles, comparing each to “usual care.” Because most United States hospitals now have sepsis protocols and are mandated to report compliance with the 3-h bundle [15–35], the 3-h bundle is a de facto proxy for usual care. In addition, because hospitals are mandated to report compliance with the 3-h bundle and because nationally compliance is moderate at 60% [42], the implementation strategy will be applied to both arms. We hypothesize that this strategy will increase compliance in both arms. Increased compliance should in turn assist sites in their efforts to comply with SEP-1.

Second, it is possible that hospitals in the 3-h arm may adopt features of the 1-h bundle, shortening the time to bundle completion and diluting the difference between the two study arms. We believe this is unlikely to be the case as the implementation strategy is designed to improve compliance with the 3-h bundle, not specifically to reduce time to treatment. In addition, it is unlikely that hospitals in the 3-h arm will develop strategies to approach the time requirements of the 1-h bundle. If 3-h hospitals do adopt implementation strategies that would target the 1-h bundle, Aim 2 analyses will allow assessment of this possibility.

Finally, by conducting the study among a diverse sample of hospitals from the Discovery Network and SCCM, we have considered issues related to generalizability. We have identified 18 hospitals and verified that none are outliers in terms of baseline compliance with the 3-h bundle. Conducting the study at hospitals of varying size and in both academic and community settings will enhance generalizability of the results.

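### The quantitative Aim 2 compliance endpoint scores each arm on its own window, so it does not measure 1-h attainment in 3-h hospitals or how far treatment times separated the arms

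*Protocol article*

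**What the plan says.** Under Compliance definition, the article lists four time-stamped elements (lactate, blood culture, antibiotics, fluids): "This study will collect the date and time associated with each of these four measures". A patient is compliant if "these date and time stamps were within 1 or 3 h (inclusive) of time zero depending on hospital randomization".

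Under Quantitative analysis of bundle compliance, "Bundle compliance will be defined as all-or-nothing for the individual elements of the bundles", and "The statistical analysis will be similar to the primary analysis for hospital mortality". That primary analysis is a random-effects logistic model with arm, period, their interaction and a random hospital term.

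The purpose of Aim 2 is worded in two ways. Study objectives hypothesises that "1 and 3-h bundle implementation compliance will be similar as assessed by" the EHR, surveys, meeting recordings and interviews. The Aim 2 heading in the Analysis plan says "Quantitative analysis will demonstrate improved compliance in both arms through the implementation strategy". Table 4 plans for 80% adherence in the 3-h arm and 70% in the 1-h arm.

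Design considerations raises the risk that 3-h hospitals complete the bundle sooner and so dilute the contrast between arms. If such hospitals take up strategies aimed at the 1-h bundle, it says, "Aim 2 analyses will allow assessment of this possibility".

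**The concern.** One compliance variable is asked to do three jobs: show improvement within each arm, show similarity between arms, and reveal 3-h hospitals drifting towards 1-h care. A window set by arm suits the first job. For the second, it compares attainment of a strict target with attainment of a lenient one. For the third, it leaves out the quantity needed, which is how often 3-h hospitals finish within 1 h.

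What is at stake is how the trial will be read. The article says that a finding of no difference would be particularly important. To interpret such a finding, one must know how far treatment times in the two arms actually differed. As written, no prespecified quantitative Aim 2 result gives that.

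**Working it through.** **1. The plan's own use of arm-specific compliance (Table 4; Recruitment and power).**
- 3-h arm: 0.80 × 18.9 + 0.20 × 26.1 = 20.34, stated as 20.3%.
- 1-h arm: 0.70 × 16.2 + 0.30 × 24.4 = 18.66, stated as 18.7%.
- Patients per hospital: 158 / 0.70 = 225.7, stated as 230. With 226 per hospital, 9 hospitals and 2 periods, 226 × 9 × 2 = 4068, stated as 4070 per arm.

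These figures reproduce. They show that 70% refers to a 1-h window and 80% to a 3-h window.

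**2. Direction of the arm gap.** Every patient who meets the 1-h window also meets the 3-h window. Attainment at 1 h therefore cannot exceed attainment at 3 h, and two arms giving identical care will score differently unless nobody finishes between 1 h and 3 h. This needs no distributional assumption.

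**3. Size of the arm gap (illustration).** The article gives no distribution of time to completion. I assume it is lognormal with median m and log-scale SD σ from 0.5 to 1.25, so that P(T ≤ t) = Φ(ln(t/m)/σ). For a given 3-h compliance c, m = 3·exp(−σ·z_c). The anchors are 60% (the national figure in the article), 80% (Table 4), and a median of 1 h. The last comes from the planned reduction of 0.25 h, stated as 25%: 0.25 / 0.25 = 1 h. It refers to antibiotics and serves here as a stand-in for the bundle.

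| Identical care in both arms | Scored at 1 h | Scored at 3 h |
|---|---|---|
| 3-h compliance 60% | 3% to 27% | 60% |
| 3-h compliance 80% | 9% to 49% | 80% |
| Median 1 h | 50% | 81% to 99% |

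The gap runs from about 31 to 71 points.

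**4. The interaction term.** Let both arms become 25% faster (m × 0.75). The ratio of odds ratios (1-h score over 3-h score) would be 1 if the interaction reflected only unequal change in care. It is 0.93 to 1.35 for the 60% and 80% anchors, and 0.50 to 0.95 for the 1-h median.

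**5. Drift in a 3-h hospital.** Start at 80% on the 3-h window and speed up by 25%. For σ = 0.5, m falls from 1.97 h to 1.48 h.
- 3-h score: Φ(ln(3/1.48)/0.5) = 92%. Over the range of σ it rises from 80% to 86–92%.
- 1-h score, not analysed: from 9% to 22% at σ = 0.5. Over the range, it rises from 9–49% to 22–58%.

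On the specified endpoint this looks like ordinary 3-h improvement.

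**6. The baseline window.** Compliance definition does not mention the baseline period, and hospitals learn their arm only after it. Read literally, 1-h hospitals are scored at 1 h in both periods. Yet the mortality model adjusts for 3-h compliance before the intervention in every hospital. If the 1-h arm were scored at 3 h at baseline and at 1 h afterwards, unchanged care at the 60% anchor would appear to fall from 60% to 3–27%.

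**7. Similarity.** No margin is stated, and the planned values differ by 10 points. For an outcome-period comparison of 80% with 70%, with 230 patients in each of 9 hospitals per arm and an assumed compliance ICC (the stated 0.025 comes from the New York database):
- ICC 0.025: design effect 1 + 229 × 0.025 = 6.725; effective n per arm 2070 / 6.725 = 308; power 82%.
- ICC 0.05: design effect 12.45; effective n 166; power 56%.
- ICC 0.10: design effect 23.9; effective n 87; power 33%.

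At the two higher ICCs, a non-significant arm term would be common (44% and 67%) even with a true gap of 10 points.

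**The case against.** The strongest defence is that Aim 2 is about fidelity. Both arms receive the same implementation package apart from bundle-specific training, so asking whether each arm reaches its own target is coherent, and an arm-specific window is the right measure for it. This stands. What it does not supply is a comparison of care between arms.

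A reader might infer that the model cannot test improvement in each arm. The documents do not support that: the model contains period and arm-by-period terms, so it gives a period effect for each arm, valid if the window is constant.

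A reader might also infer that Aim 2 cannot detect contamination at all. That goes too far. The statement in Design considerations is conditional on 3-h sites adopting 1-h strategies, and the coded collaborative meetings and the interviews can show this. Time stamps are collected without restriction by arm, and Table 1 lists minutes to antibiotics for both arms. Nor is a null mortality result left wholly uninterpretable, since the fifth subgroup analysis relates time to treatment to mortality in both arms. But the qualitative data do not measure how far treatment times separated, and that subgroup analysis does not compare treatment times between arms.

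Finally, one might try to size the compliance contrast from the plan's targets by backing out a baseline 3-h compliance of (26.1 − 23.2)/(26.1 − 19.1) = 41%. This applies a post-intervention mortality for non-compliant patients to the pre-intervention period, and a 1-h baseline would still have to be assumed. I do not rely on it.

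The analysis plan is not shown and may add tables or a margin. The point here is that the article states a rule and a claim about contamination that do not fit together.

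**Conclusion.** The point holds as a limited fault in the stated endpoint, not in the data. The between-arm terms of the Aim 2 compliance model mix two windows, and 1-h attainment in 3-h hospitals is not measured. The claim that Aim 2 will allow assessment of drift towards 1-h care is supported only by the qualitative process data. The direction of the arm gap under identical care is certain. Its size, about 31 to 71 points, and the interaction ratios of 0.50 to 1.35 rest on the assumed lognormal times.

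Within-arm change is sound provided one window is used throughout, which the article should say. Similarity cannot be read from a non-significant term, given a planned 70% against 80% and no margin.

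The primary mortality analysis is by intention to treat and does not use this variable; its only compliance input is 3-h compliance before the intervention, as a covariate. This is a worthwhile clarification and not a must-fix.

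**What to change.** - Score every patient in both arms and both periods at both 1 h and 3 h, from the time stamps already collected.
- Keep within-arm change on the assigned window as the test of improvement, and state that the window is the same at baseline and outcome.
- Prespecify the between-arm differences in 1-h attainment and in time to antibiotics as the measure of separation and contamination, and refer to them under Design considerations.
- Report the between-arm compliance difference with a confidence interval in place of an inference of similarity. If similarity is to be claimed, set a margin in advance and reconcile it with the planned 70% and 80%.

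The cost is wording and a small amount of extra analysis. No new data, patients or site work are needed.

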##### Subgroup analyses

A second sensitivity analysis will follow the statistical plan for the primary intention to treat analysis but use triage time as the time of presentation (“time zero”), and a third sensitivity analysis will also follow the intention to treat analysis strategy but count discharge to hospice as a death. A fourth sensitivity analysis will examine only patients who received therapies after the time of presentation to more properly evaluate the impact of therapies initiated in the hospital (e.g., excluding patients assigned credit for fluids or antibiotics administered prior to arrival to the hospital). A fifth subgroup analysis will examine the impact of time to treatment on mortality in both study arms using time as a continuous variable.

##### Secondary outcomes

Four secondary outcomes will be investigated: respiratory failure requiring mechanical ventilation, the number of ventilator-free days, and hospital and ICU length of stay. The same statistical approach described in the primary analysis will be used here; however, the analysis for the count of ventilator-free days will be based on random-effects negative binomial regression or a zero inflated negative binomial regression, depending on the distribution of the count of ventilator-free days. Similar to hospital mortality, the requirement for mechanical ventilation will be based on random-effects logistic regression. Hospital length of stay analysis will be based on a random-effects linear regression. However, prior to the analysis, length of stay will be normalized using the natural logarithm since this variable is not normally distributed. After running the random-effects linear regression, the results will be back transformed to the original units producing the ratio of the geometric mean length of stay for patients in one arm compared to the other arm.

#### Aim 2: Quantitative analysis will demonstrate improved compliance in both arms through the implementation strategy and qualitative analyses will provide insights into implementation strategy effectiveness

Surveys assessing implementation-related constructs will be completed at baseline (Exploration phase) and then repeated during the Sustainment phase. We will conduct within-subjects Wilcoxon signed rank test with the survey data, examining changes over time.

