## Methods

### Study design

This study is a pragmatic, cluster-randomized trial of 18 hospitals (9 in each arm) comparing the 1- and 3-h bundles in patients presenting to emergency departments (ED) with sepsis. We will use a hybrid type 2 effectiveness-implementation design [46] to evaluate (1) effectiveness outcomes, including mortality and respiratory failure, and (2) implementation outcomes, including compliance (Fig. 1). The multi-faceted implementation strategy will apply to both trial arms. Application of the Pragmatic Explanatory Continuum Indicator Summary [47–50] (PRECIS) tool identifies this trial as pragmatic (vs. explanatory) [51]. A cluster-randomized trial is appropriate for analyzing the comparative effectiveness of the 1-h bundle versus the 3-h bundle because of the impossibility of randomizing patients to a particular approach and the importance of implementation of bundles at the hospital level. This protocol adheres to the Standard Protocol Items: Recommendations for Interventional Trials (SPIRIT) guidelines [52]. Figure 2 provides a summary of the enrollment schedule, interventions, and assessments using the SPIRIT flow diagram.

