### Randomization

Hospitals will be randomized to one of two arms (1- or 3-h bundle) in a 1:1 ratio. Randomization will be accomplished using randomly permuted blocks of variable size and controlling for academic or community status. Hospital physician and nurse dyads will be told which condition they were randomized to during in-person meetings at SCCM immediately prior to the Implementation Phase; separate meetings will take place for each study arm. Each arm will undergo a 30-month structured, collaborative implementation approach to operationalize compliance with their bundle assignment. The elements of both bundles are identical—only the timing is different (see Table 1). In this cluster-randomized clinical trial, the hospital is the unit of randomization. Hospitals will be informed as to their randomized arm after the baseline collection period. The randomization will be done by the study statistician and held only in the statistician’s computer until the reveal meeting at the end of the baseline period. Due to the pragmatic, open-label design of this trial and its objective measurement of study outcomes, the study staff, investigators, sites, and biostatisticians will not be masked to treatment condition once randomization occurs. Patients will receive standard of care for sepsis and their data will be collected retrospectively by the hospital each month.

**Table 1 Tab1:** 1- and 3-h bundle elements: quality and outcome indicator definitions and specifications

	**Definition of bundle element (quality indicator) or outcome measure obtained from the EHR by site staff**	**Both study arms**

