#### ***Exploration phase (6 months) (***Fig. 1***)***

##### Assess for readiness, organizational culture, and barriers and facilitators

Prior to implementation, sites will participate in formative evaluations [55], which will involve: First, *surveys with ED leadership* (physician and nurse dyads) to explore leadership and team attitudes and engagement, assess their needs related to sepsis bundle adoption, explore anticipated barriers to implementation, and identify potential facilitators of change. We will use several scales during the exploration phase, and then again at the conclusion of the Implementation phase: (a) Implementation Leadership Scale (ILS) [56]; (b) Evidence-Based Practices Attitudes Scale (EBPAS-15) [57]; (c) Organizational Readiness for Implementing Change (ORIC); and (d) Implementation Climate Scale (ICS) [58]. Secondly, *semi-structured interviews with key ED informants* will occur during the formative, process, and summative evaluation phases [59]. Leaders, physicians, nurses, and other hospital staff will be asked about their openness/resistance to change generally and to the use of sepsis bundles, beliefs about the evidence supporting sepsis bundles, perceptions of the utility of the bundles, fiscal obstacles (or facilitators), and beliefs about the importance of timely treatment.

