### Analysis plan

#### Aim 1: 1-h bundle will have significantly lower patient mortality and improve all secondary outcomes

##### Primary outcome analysis

An intention to treat analysis of patient mortality in each arm will be evaluated in 2 ways: (1) the difference, in primary outcomes (hospital mortality), between the two arms during the 6-month baseline assessment and the 6-month outcomes assessment, and (2) the comparison between the first two differences (i.e., difference-in-difference estimation). This difference-in-difference analysis will be the *primary analysis* to assess the *primary hypothesis* of Aim 1: the 1-h bundle will result in lower mortality than the 3-h bundle. Both absolute and risk-adjusted hospital mortality will be reported. Random-effects logistic regression will evaluate all the mortality differences. The random term will be the hospital. This model will contain three binary risk factors: (1) 1-h arm vs. 3-h arm, (2) 6-month baseline period prior to randomization vs. 6-month outcome assessment phase, and (3) the interaction of these two terms. The effect of the intervention and the effect of the two time periods will be quantified by odds ratios while the differences in hospital mortality will be quantified by model probabilities. Additionally, the model will be adjusted for hospital level 3-h bundle compliance prior to intervention along with patient and hospital characteristics.

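### The Aim 2 survey test ignores the hospital: an individual-level signed-rank test on paired leaders from 18 sites rejects too often if their changes correlate positively

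*Protocol article*

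**What the plan says.** The Aim 2 part of the Analysis plan (Protocol article) names a single method for the implementation surveys: "We will conduct within-subjects Wilcoxon signed rank test with the survey data, examining changes over time".

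The section on assessing readiness, culture, barriers and facilitators says who answers. The surveys go to ED leadership, described as "physician and nurse dyads) to explore leadership and team attitudes and engagement". The scales given before and after are the ILS, EBPAS-15, ORIC and ICS. Study design sets the number of sites: "This study is a pragmatic, cluster-randomized trial of 18 hospitals (9 in each arm".

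On timing, the Aim 2 text says "Surveys assessing implementation-related constructs will be completed at baseline (Exploration phase) and then repeated during the Sustainment phase", while the readiness section says "We will use several scales during the exploration phase, and then again at the conclusion of the Implementation phase". The small difference between these does not affect the point made here.

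Elsewhere the hospital is taken into account. For mortality, "The random term will be the hospital". The Secondary outcomes section uses random-effects models in the same way, and for bundle compliance "The statistical analysis will be similar to the primary analysis for hospital mortality".

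**The concern.** The signed-rank test takes its null distribution from independent differences. Here the differences come in pairs from the same emergency department. Both leaders work under one site programme: "Each arm will undergo a 30-month structured, collaborative implementation approach", with a shared change team, learning collaborative and monthly feedback. A programme that takes hold at one site and stalls at another would move both leaders' scores together. The effective number of independent observations would then be smaller than the number of people, and the p-value would be too small.

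At stake is the reliability of statements that leadership, climate, readiness or attitudes changed over the study. The Study objectives list surveys among the four sources for the Aim 2 hypothesis, and all four scales would be tested in the same way.

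**Working it through.** The article gives no sample size, power or error rate for the surveys, so there is no stated figure to reproduce. The check is the true type I error of the named test.

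**Inputs from the article**
- Hospitals: H = 18 (Study design).
- Respondents per hospital: m = 2, one physician and one nurse (readiness section). One pair per site gives 18 × 2 = 36 people. This total is derived, not stated.

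**Assumptions**
- Two-sided 5% level. The article states α = 0.05 only for the mortality power calculation.
- Within-hospital correlation ρ of the change scores: not given, so a range of 0 to 0.5 is used. The article's ICC of 0.025 is for patient mortality and does not carry over to staff surveys.
- All 36 people answer twice, and there is no true change.

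**Formula**
- Design effect: D = 1 + (m − 1)ρ = 1 + ρ for pairs.
- Approximate true error: 2 × [1 − Φ(1.96/√D)].
- Example at ρ = 0.3: D = 1.3, and 2 × [1 − Φ(1.96/√1.3)] = 8.56%.

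**Results.** The simulations use 20,000 null data sets per row, normal change scores and the normal approximation to the signed-rank statistic. The Monte Carlo standard error near 5% is √(0.05 × 0.95/20,000), about 0.15 percentage points.

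| ρ | D | Formula, 36 people | Simulated, 36 people | Simulated, 18 hospital means |
|---|---|---|---|---|
| 0 | 1.00 | 5.00% | 5.03% | 4.81% |
| 0.05 | 1.05 | 5.58% | 5.42% | 4.85% |
| 0.1 | 1.10 | 6.17% | 6.22% | 4.74% |
| 0.2 | 1.20 | 7.36% | 7.48% | 5.11% |
| 0.3 | 1.30 | 8.56% | 8.46% | 4.94% |
| 0.5 | 1.50 | 10.95% | 10.74% | 4.76% |

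Formula and simulation agree. The test on hospital means stays between 4.7% and 5.1% throughout.

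**Negative correlation.** By the same formula the individual-level test is conservative: 3.9% at ρ = −0.1 and 2.8% at ρ = −0.2.

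**Departures.** Suppose each leader is still present at the second survey with probability r, independently. About 36r people and 18r² complete pairs then remain, so the variance of the summed changes is proportional to 36r + 2 × 18r²ρ = 36r(1 + rρ), and D = 1 + rρ. At an assumed r = 0.5 and ρ = 0.3, D = 1.15 and the error is about 6.8% instead of 8.5%. Only 18 × 0.25 = 4.5 hospitals would keep a complete pair.

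**The case against.** The strongest objection is that a reader may infer inflation from the wrong fact. Climate, readiness and leadership belong to the department, so two leaders should score alike. But that concerns levels. The test uses each person's own difference, in which any stable hospital level cancels. Only shared change produces clustering, and the article gives no value for it. This objection stands. It makes the inflation conditional, and it rules out saying flatly that the p-values are too small. The argument for shared change is also weaker for the EBPAS-15, which measures the respondent's own attitudes.

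Second, with only two people per site the effect is modest over much of the plausible range. Quoting only correlations of 0.3 and above would overstate it. This stands too, so the full range is shown.

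Third, a reader might infer that the surveys will describe only leaders who stayed, since the two rounds are at least 6 + 30 = 36 months apart and the test needs the same person twice. The article does not support this as a finding. It gives no turnover rate. It has a general sentence on multiple imputation in the power section, although that is not tied to the surveys. The handling of replaced respondents is a detail that an article commonly leaves to the full protocol or SAP. Nor can heavy turnover be added to the error rates for complete pairs, because departures break up pairs and shrink the clustering.

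None of this removes the mismatch itself. The test is named, it assumes independence, the respondents are paired within hospitals, and the article's other outcome analyses for Aims 1 and 2 account for the hospital.

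**Conclusion.** The point holds as a minor one. As written, the survey test does not respect the clustering of respondents within hospitals. If change scores correlate positively within a hospital, a nominal 5% test has a true error of about 5.4% to 10.7% for correlations of 0.05 to 0.5.

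These figures rest on one pair of leaders per site, complete responses at both rounds, and a correlation that is assumed. There is no inflation at zero correlation, less with incomplete pairs, and conservatism if the correlation is negative.

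The surveys are supporting data, used alongside electronic-record compliance, meeting recordings and interviews. The Aim 2 hypothesis is that compliance will be similar in the two arms, and no decision rule is attached to a survey score. The mortality and quantitative compliance analyses already use a random hospital effect and are unaffected.

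**What to change.** In the Aim 2 analysis text, make the hospital the unit of the survey test. Compute each respondent's change, average the changes within the hospital, and run the Wilcoxon signed-rank test on the 18 hospital-level values. A cluster-adjusted signed-rank test on individual changes would also serve. Either keeps the within-person question that the protocol poses.

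A linear mixed model with time as a fixed effect and random effects for hospital and person, using every respondent at either round, may be added as a sensitivity analysis.

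The cost is a few lines of text and no new data. The effective sample becomes 18 hospitals, so intervals may be wider, and a hospital that loses both leaders contributes nothing to the main test. The all-respondent model mixes change within people with replacement of one respondent by another, so it answers a somewhat different question and should not replace the main test.
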